## Abstract

**Background:**

Conduct disorder (CD) is a complex mental disorder characterized by severe rule-breaking and aggressive behavior. While studies have shown that several therapeutic interventions are effective in treating CD symptoms, researchers call for treatments based on etiological knowledge and potential patho-mechanisms. Mentalization-based treatment (MBT) may represent such a treatment approach: Studies have shown that individuals with CD show mentalizing deficits and that mentalizing might represent a protective factor against the development of the disorder. As MBT focuses on the understanding of social behavior in terms of mental states, fostering mentalizing might help CD individuals to (re)gain an adaptive way of coping with negative emotions especially in social interactions and thus reduce aggressive behavior. For this purpose, MBT was adapted for adolescents with CD (MBT-CD). This is a protocol of a feasibility and pilot study to inform the planning of a prospective RCT. The primary aim is to estimate the feasibility of an RCT based on the acceptability of the intervention and the scientific assessments by CD individuals and their families indicated by quantitative and qualitative data, as well as based on necessary organizational resources to conduct an RCT. The secondary aim is to investigate the course of symptom severity and mentalizing skills.

**Methods:**

The bi-center study is carried out in two outpatient settings associated with university hospitals (Heidelberg and Mainz) in Germany. Adolescents aged between 11 and 18 years with a CD or oppositional defiant disorder (ODD) diagnosis are included. Participants receive MBT-CD for 6 to 12 months. The primary outcome of the feasibility study (e.g., recruitment and adherence rates) will be descriptively analyzed. Multilevel modeling will be used to investigate secondary outcome data.

**Discussion:**

Fostering the capacity to mentalize social interactions triggering non-mentalized, aggressive behavior might help CD individuals to behave more adaptively. The feasibility trial is essential for gathering information on how to properly conduct MBT-CD including appropriate scientific assessments in this patient group, in order to subsequently investigate the effectiveness of MBT-CD in an RCT.

**Trial registration:**

ClinicalTrials.gov, NCT02988453. November 30, 2016

**Recruitment status:**

Recruitment complete and intervention complete, follow-up assessments ongoing (Heidelberg). Recruitment and assessments ongoing (Mainz).

**Recruitment country:**

Germany

**Health condition studied:**

Conduct disorder, oppositional defiant disorder

**Intervention:**

Mentalization-based treatment for conduct disorder (MBT-CD): MBT-CD is an adaptation of MBT for Borderline Personality Disorder. This manualized psychodynamic psychotherapy focuses on increasing mentalizing, i.e., the ability to understand behavior in terms of mental states, in patients. MBT-CD includes weekly individual sessions with the patient and monthly family sessions.

**Key inclusion and exclusion criteria:**

Included are adolescent individuals with a diagnosis of conduct disorder or oppositional defiant disorder aged between 11 and 18 years.

**Study type:**

Feasibility and pilot study (single-group)

**Date of first enrollment:**

19.01.2017

**Study status:**

The trial is currently in the follow-up assessment phase in Heidelberg and in the recruitment and treatment phase in Mainz.

**Primary outcomes:**

Acceptability of MBT-CD intervention (as indicated by recruitment rates, completion rates, drop-out rates, treatment duration, oral evaluation), acceptability of scientific assessments (as indicated by adherence, missing data, oral evaluation), and necessary organizational resources (scientific personnel, recruitment networks, MBT-CD training and supervision) to estimate feasibility of an RCT

**Secondary outcomes:**

Adolescents’ symptom severity and mentalizing ability

**Protocol version:**

20.08.2020, version 1.0

**Supplementary Information:**

The online version contains supplementary material available at 10.1186/s40814-021-00876-2.

## Background and rationale

Conduct disorder (CD) is a severe and complex mental disorder most common in adolescence. It is defined as a “repetitive and persistent pattern of behavior in which the basic rights of others or major age-appropriate societal norms or rules are violated” [1]. Epidemiological studies have shown that about 5-10% of all children and adolescents meet the criteria for CD, while boys are more likely to be diagnosed than girls [2]. CD is a serious risk factor for the development of antisocial personality disorder (ASPD). More than 50% of men with ASPD fulfilled criteria for CD prior to the age of 15 [3]. Moreover, CD is often comorbid with attention deficit hyperactivity disorder [4] and is associated with an increased risk for the development of a number of other mental disorders, including anxiety disorders, depression, substance use disorder, and bipolar disorder [5]. The following environmental factors have been identified to be associated with an increased risk for the development of CD [6]: dysfunctional parent-child interactions, critical life events such as parental divorce, parental loss, as well as early neglect, physical and sexual abuse [6–8]. The accumulation of risk factors further increases the risk for the development of CD [9]. At the same time, protective factors like intelligence or social support can help reduce the risk for dysfunctional development [10]. Based on these findings, there is consensus that the emergence of CD is complex [11], yet still, very little is known about the mechanisms contributing to the development and maintenance of CD subsequent to the exposure to the identified risk factors.

So far, meta-analyses have shown that a number of interventions are effective in reducing CD symptoms [12, 13]. Among these, cognitive-behavioral therapy, social skills training, parent training, and multi-systemic therapy are regarded as evidence-based treatments [12, 14]. They differ in their involvement of parents or peers, but their focus on CD symptom management is common to all. However, effect sizes are small, conduct problems oftentimes persist and it remains unclear which treatment works best for whom and why [12]. Moreover, drop-out rates of around 20% [12] and low motivation to seek treatment in the first place render the effective and sustainable treatment of CD pathology difficult. Importantly, interventions are so far lacking a comprehensive etiological understanding of CD, which may entail the failing of targeting relevant mechanisms contributing to the development and maintaining of CD symptoms. In line with this notion, authors call for specification of interventions to target specific individual or subgroup deficits [11, 12] and base them on knowledge about underlying patho-mechanisms [11].

Recently, it has been shown that CD alongside many other mental disorders is related to dysfunctions in mentalizing [15]. Mentalizing describes an individual’s imaginative ability to perceive one’s own and other’s behavior as the product of affective and cognitive mental states [16]. [name] and colleagues [17] showed that adolescents with CD have a significantly lower mentalizing capacity compared to adolescents with no CD. These findings were replicated in a later study by Cropp et al. [18]. Moreover, focusing more on a developmental perspective fostering insight into possible patho-mechanisms, studies showed that mentalizing mediates the relationship between childhood maltreatment and externalizing problems: [name] and colleagues [19, 20] found that mentalizing (partially) mediated the relationship between childhood maltreatment and potential for violent behavior in adolescence (14-21 years, [19]; 15-18 years, [20]). Similarly, Ensink and colleagues [21] found that mentalizing partially mediated the link between childhood sexual abuse and externalizing problems, such as rule-breaking and aggressive behavior, in children aged between 7 and 12. Moreover, investigating adolescent PTSD patients, Abate and colleagues [22] found that hyper mentalizing mediated the link between trauma and aggression in female PTSD inpatients. Taken together, results indicate that mentalizing may serve as a protective factor against externalizing behaviors while dysfunctional mentalizing may not only be part of CD pathology but also etiology.

The relation between limited (inhibited or biased) mentalizing and aggressive behavior in CD may be explained by different phenomena: Firstly, if mentalizing is inhibited, the “violence inhibition mechanism” as described by Blair [23] might be impaired: According to the author, violent behavior is normally inhibited when we see and empathize with others’ distress. If however mentalizing is inhibited, and consequently, individuals have difficulties to recognize others’ distress, the threshold for aggression and violent behavior might be lowered. Secondly, if mentalizing is negatively biased, aggressive behavior may be elicited due to a more hostile “social information processing” [24–26] in these adolescents, characterized by a tendency to attribute hostile intent upon neutral or even positive social signals. As we can train and change the capacity to mentalize, a treatment focusing on enhancing mentalizing might thus be able to target a relevant patho-mechanism of CD.

In sum, we assume that a psychological intervention with a focus on improving mentalizing in the adolescent and his/her family can improve CD pathology as effective or even more sustainably than interventions focusing on symptom management only.

For this purpose, the authors have developed mentalization-based treatment (MBT) for CD (MBT-CD). MBT-CD is a further development of MBT, which is evidence-based for patients with borderline personality disorder. MBT has already been adjusted successfully to working with adolescents with self-harm [27]. MBT-CD focuses on the development of a basic understanding of interpersonal situations and emotions, and specific mentalizing deficits that trigger antisocial and aggressive behavior. In order to make this new treatment available for the adolescent population, we need to determine its effectiveness by conducting a randomized controlled trial (RCT). In line with the SPIRIT ([28], for an overview of included items please see Additional file 1) and Consolidated Standard of Reporting Trials (CONSORT) statement [29], this protocol of a feasibility study is aimed at enhancing transparency and quality in gathering information to develop and appropriately conduct the protocol of a future RCT.

## Methods/design

### Aims

The primary aim of the feasibility and pilot study is to estimate the feasibility of an RCT on MBT-CD based on acceptability of the intervention (indicated by recruitment rates into treatment, drop-out rates and completer rates, and adolescents’ oral evaluation), acceptability of the scientific assessments by the patients and family (indicated by adherence rates to the scientific assessments, and adolescents’ oral evaluation), and organizational resources needed to conduct an RCT in an outpatient only and a combined outpatient and inpatient setting in the future. The secondary aim is the examination of CD-symptom severity over time, the course of aggressive and antisocial behavior, and changes in mentalizing. The primary aim of the future RCT will be to determine the effectiveness of MBT-CD in terms of CD symptom severity, levels of aggression, and antisocial behavior as well as an appropriate comparison group. The secondary aim of the RCT will be to investigate the change in a proposed patho-mechanism (i.e., mentalizing) and general symptom severity through MBT-CD.

### Design

The study is a feasibility and pilot trial to form the basis for a future, prospective RCT. The study is carried out at two treatment centers in Heidelberg (Institute for Psychosocial Prevention) and Mainz (Pediatric and Adolescent Psychiatry Mainz), Germany. Adolescent participants receive MBT-CD over the course of 6 to 12 months. Adolescents and their parents are asked to take part in study assessments every 3 months during treatment and 3 months after the end of treatment (for an overview of study flow see Fig. 1). The design is adaptive in that both, intervention and scientific assessments can be changed in the course of the study, if, e.g., drop-out rates and reasons indicate necessary adjustments for successful study continuation. Originally, this feasibility trial was designed as a single-blinded RCT to test the effectiveness of MBT-CD compared to treatment as usual (TAU) delivered as an outpatient treatment at the Clinic of Child and Adolescent Psychiatry at the University-Hospital Heidelberg. This comparison group was chosen as it is in line with the routine health care treatment for adolescents with CD [30]. Due to recruitment problems identified in yearly interim recruitment analyses, the design was changed into a non-randomized single group feasibility and pilot trial. This decision was made in consensus with the study funders (Dietmar-Hopp-foundation and Heidehof foundation) upon fulfilling the study termination criterion of recruiting less than 20% of the a priori estimated overall sample size of 102 adolescents within 1 year (to detect a medium effect and considering 25% drop-out).

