### Statistical analysis

All analyses will be performed according to the intention to treat principle. Analyses on quantitative data will be conducted using the statistical software SPSS (IBM, Version 25). Sociodemographic data and data of the scientific assessments at baseline (T1, see Table 1) will be used to characterize the sample. Primary outcome variables (recruitment rates, drop-out rates, and missing data of adolescents as well as parents) will be descriptively analyzed. The distribution of treatment duration (in months and number of sessions) will be analyzed to infer the optimal dose of treatment and necessary flexibility in treatment dose and duration. Scientific personnel costs will be estimated based on timely effort (hours needed per month, total number of months). Secondary outcome variables will be investigated using multilevel modeling. Content analysis will be used to investigate qualitative data (drop-out reasons, oral evaluations of MBT-CD, and the scientific assessments). As additional subgroup analysis, binomial logistic regression will be conducted modeled after Jorgensen and colleagues [56], who identified low RF, but not clinical or sociodemographic variables to predict drop-out of MBT group treatment in adolescents with borderline personality disorder. Data entry will be double checked and range checks for data values will be conducted. Pseudonymized data will be anonymized as soon as possible. Anonymized data will be stored in Heidelberg according to the European GDPR [51] and deleted 10 years after study completion.

**Table 1 Tab1:** Overview of the scientific assessments and time points in both settings

		Measure	T1^a^	T2^b^	T3^c^	T4^d^
Adolescent		WAI-SR		X	X	
		STAB	X	X	X	X
		RPQ	X	X	X	X
		YPI	X			
		CFT-2	X			
		LoPF-Q 12-18	X		X	X
		MASC	X		X	
		RFQ-8	X		X	X
		ECR-RC	X		X	X
		ERQ	X		X	X
		ZKE	X		X	
		BRFI	X		X	
		CECA-Q	X			
		M.I.N.I KID	X		X	
		SCID-II	X		X	
		CGI-SI	X		X	
		SCL-90-R	X		X	
		DAPP-BQ	X			
		GAF	X		X	
		CSSRI-EU	X	X	X	X
Parent		SIPA	X		X	X
		RFQ-8	X		X	X
		WAI-SR		X	X	
		ECR-R	X		X	

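### The aim is feasibility of an RCT, but the single-group outcomes cannot show acceptance of randomisation or a comparator, and the RCT phase's recruitment failure is left out of the judgement

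*Protocol article*

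**What the plan says.** The Aims section states: "The primary aim of the feasibility and pilot study is to estimate the feasibility of an RCT on MBT-CD". It names the basis as acceptability of the intervention, acceptability of the assessments, and organisational resources, and it looks ahead to an RCT "in an outpatient only and a combined outpatient and inpatient setting in the future". The Primary outcomes section repeats this basis and lists the measures under each of the three heads.

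The Design section says that the trial began as a single-blinded RCT against treatment as usual (TAU), with TAU delivered in Heidelberg. It goes on: "Due to recruitment problems identified in yearly interim recruitment analyses, the design was changed into a non-randomized single group feasibility and pilot trial". The trigger was a termination criterion of "recruiting less than 20% of the a priori estimated overall sample size of 102 adolescents within 1 year". The target of 102 was set for a medium effect with 25% drop-out. The same section adds: "The design is adaptive in that both, intervention and scientific assessments can be changed in the course of the study".

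On analysis, the Statistical analysis section says: "Primary outcome variables (recruitment rates, drop-out rates, and missing data of adolescents as well as parents) will be descriptively analyzed". At the time of the article, Heidelberg had finished recruitment and Mainz was still recruiting.

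**The concern.** An RCT asks two things of families that a single-group study does not: to let chance decide the treatment, and to accept the comparator if allocated to it. After the design change nobody is asked either. A recruitment rate into treatment then measures consent to guaranteed MBT-CD, which is a different quantity from consent to a randomised comparison.

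The trial does hold evidence on the second quantity, and it is adverse: recruitment under the RCT design fell below the trial's own floor. That result is not among the primary outcomes, and the analysis section does not mention it. The Discussion, in listing why an RCT may be hard in these patients, names low help-seeking and drop-out but not this result.

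At stake is the main conclusion. A favourable single-group rate could be read as support for an RCT when the only attempt at one stopped for lack of recruits.

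**Working it through.** **1. Inputs from the documents (Design section).** Planned RCT size 102; termination criterion below 20% of that in 1 year, met; planning drop-out 25%. Recruitment counts, screening counts and a target size for the current study are not given.

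**2. The plan's own figure of 102.** Alpha, power, sidedness and test are not stated, so the figure cannot be reproduced. Assuming d = 0.5, 1:1 allocation, alpha 0.05, 80% power and a t-test:
- two-sided: 128 in total, and 128/0.75 = 171 with drop-out;
- one-sided: 102 in total, and 102/0.75 = 136 with drop-out.

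A baseline-adjusted model with about 76 completers (102 × 0.75 = 76.5) would also fit, given a baseline correlation of about 0.63 (two-sided) or 0.48 (one-sided). The figure is neither confirmed nor called wrong. It serves below only as the stated target.

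**3. What the met criterion implies.** 0.20 × 102 = 20.4, so at most 20 recruits in the year. Time to 102 at that ceiling: 102/20 = 5.1 years. The true count may be lower: 15 a year would give 102/15 = 6.8 years, and 10 a year 102/10 = 10.2 years (both rates assumed).

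**4. What the listed outcomes can answer.**

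| Question for an RCT | Listed primary outcome |
|---|---|
| Do families take up MBT-CD? | Recruitment and consent rates |
| Do they stay in it? | Completion, drop-out and reasons, duration, sessions, oral evaluation |
| Do they complete the assessments? | Adherence, missing data, preferred mode, oral evaluation |
| Can the centres run it? | Personnel, networks, training and supervision |
| Do families accept random allocation? | None |
| Do they accept and stay in a comparator? | None |

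**5. What pooling could do (illustration; all rates assumed).** Take 12 randomised months at 1.5 a month (18 a year, under the 20.4 limit) and 24 single-group months at 3 a month. The pooled rate is (12 × 1.5 + 24 × 3)/36 = 90/36 = 2.5 a month. Projected time to 102 is 102/2.5 = 40.8 months, against 102/1.5 = 68 months from the randomised phase alone.

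For consent, assume 20% of 50 screened consent under randomisation and 60% of 50 to 100 under open treatment. The pooled rate is (10 + 30)/100 = 40% to (10 + 60)/150 = 47%, about twice the randomised-phase figure.

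**6. Precision of a drop-out rate near 25% (exact 95% CI; sample sizes assumed).**

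| Drop-outs/n | 95% CI |
|---|---|
| 5/20 | 9 to 49% |
| 8/30 | 12 to 46% |
| 10/40 | 13 to 41% |
| 15/60 | 15 to 38% |

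Every interval contains both the 25% planning figure and the roughly 20% that the Background cites from the literature. A bare percentage would say little about either.

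**The case against.** The strongest reply is that the documents are open about the change and define feasibility through acceptability and resources. Intervals, breakdowns by phase and similar detail normally belong in an analysis plan that is not shown. The part about detail stands: a missing interval or stratification would not be a finding on its own. It does not answer the main point, because the article states positively what feasibility will be estimated from, and that basis leaves out what distinguishes an RCT from the present study.

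Four stronger readings are tempting, and the documents do not support them.
- A reader might infer that the phases will be pooled and the RCT evidence thereby diluted. The analysis section says only that the rates are descriptive. Pooling is a risk, not a stated plan.
- A reader might infer that no result could count against feasibility. The article sets no level of any outcome that would mean not feasible. But poor rates, drop-out reasons, oral evaluations or resource needs could still be read as adverse, and the met termination criterion already is an adverse result.
- A reader might infer that families refused randomisation or TAU. The Design section speaks of recruitment problems without giving a cause. Low motivation and little help-seeking, which the article also cites, would hinder a single-group study too.
- A reader might take the 20% and 25% figures as ready-made success thresholds. The first is a stopping floor: recruiting at exactly 20% of target a year still means five years. The second is a sample-size allowance, not a limit of acceptability.

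It is also fair that one randomised phase against outpatient TAU need not predict an RCT in other settings or with another comparator, which the Aims leave open. That phase is the main evidence on RCT recruitment, not the sole basis for it.

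**Conclusion.** The concern holds in this form. The stated basis for judging RCT feasibility cannot by itself support a conclusion about randomisation or a comparator, and the one RCT-phase result is not carried into that judgement.

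The firm figure is at most 20 recruits in a year, hence at least 5.1 years to 102. It assumes that the original target and the rate at that time still apply; another target, comparator or number of centres would change it. The contrast of 41 with 68 months and the 40 to 47% consent rate rest wholly on assumed rates and on pooling that the text does not state, so they show direction only. The drop-out intervals are exact for the assumed sample sizes.

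**What to change.** In the Primary outcomes and Statistical analysis sections:
1. Report recruitment, consent and drop-out separately for the Heidelberg randomised phase, the Heidelberg single-group phase and Mainz, with exact 95% CIs and the date of each adaptation marked. The text places TAU in Heidelberg; if Mainz also randomised, split it in the same way.
2. Count the met termination criterion as a feasibility result. Use the randomised-phase rate as the main evidence on RCT recruitment, with reasons for refusal where they were recorded.
3. State that single-group rates cannot by themselves show acceptance of randomisation or TAU.
4. Add one question at consent in Mainz on willingness to be randomised. It measures stated intention only, but no listed outcome now covers the point.
5. Do not use the 20% floor or the 25% allowance as success thresholds. Show the drop-out interval beside 25% only to inform planning of the RCT.

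The cost is some analysis wording and one extra question. The downside is smaller numbers per stratum, wider intervals and a less favourable headline rate. Refusal reasons from the closed Heidelberg phase can be used only if they were noted at the time.
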